**C.3.c.3. Other factors potentially related to physical activity**. We will measure the perceived benefits of physical activity using the HINTS survey items.^125^ This instrument asks participants: (1) As far as you know, does physical activity or exercise increase the chances of getting some types of cancer, decrease the chances of getting some types of cancer, or does it not make much difference? (2) Can exercise help to lower the chances of getting some types of cancer or does exercise not make much difference? We will also administer the International Physical Activity Prevalence Study environmental module which queries participants about their neighborhood and its walkability as well as access to physical activity and recreation facilities. We will assess perceived neighborhood safety by asking participants, “how safe is the neighborhood you live in during the daytime?” We will also ask about the safety of the neighborhood they live in at night and the neighborhood they work in. Response options will be “safe”, “a little unsafe” and “not at all safe”. In previous work by the research team, these questions were associated with daily step count.^126^ Additional items on stress ^127-131^, neighborhood environment ^132, 133^, depression^134^, and coping mechanisms^135^ will also be included on the questionnaire.

**C.3.c.3. Other measures.** The baseline and follow-up questionnaires will also query sociodemographic variables (age, race/ethnicity, gender, education, household income, current occupation), family history of colon cancer, current and past tobacco use, diet and supplement use (using the Willett food frequency questionnaire) and use of hormones (in women).

**C.4. Randomization.** Following the baseline assessment, study staff will assign participants to an intervention condition using a random numbers program. An equal number of individuals will be assigned to each condition (10 low dose, 10 high dose). Staff doing the randomization will not participate in the eligibility screening or baseline assessment and will not have access to information about participants.

**C.5. Intervention.** Following the baseline assessment, participants will be randomly assigned to one of two doses of physical activity delivered through the First Step program.

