**C.9. Sample size and power considerations for primary outcomes.** Schmitz et al found baseline insulin in the control group to be 4.46 (+/- 0.59) uU/ml and in intervention subjects to be 5.18 (+/- 0.54) uU/ml in an exercise study.^67^ Over 39 weeks of exercise intervention, insulin increased an average of 1.16 uU/ml in the control group and 0.05 uU/ml in the intervention group, for a net intervention effect of 1.1 uU/ml. Using this data, the sample size to achieve 85% power for the primary comparison of insulin change over 12 months between the intervention and control groups using a Bonferroni correction with two-sided 0.05/2 = 0.025 and an estimated correlation over 39 weeks for insulin of 0.5 is n = 2σ^2^_change_ (Z_0.9875_ + Z_0.85_)^2^/ Δ^2^

where σ^2^_change_ = 2 σ^2^_baseline_ (1 – ρ) = 123.63, σ^2^_baseline_ = 0.59^2^, ρ = 0.5, Z_0.9875_ = 2.24, Z_0.85_ = 1.035, and Δ = 1.1 This yields a sample size of 6 subjects per group.

The estimates of change for insulin are comparable to the difference between the highest and lowest quintiles of physical activity in the Nurses’ Health Study (difference = 1.37 μU/ml) and the Health Professionals’ Follow-up Study (difference = 2.4 μU/ml).^68^ The difference in C-peptide between highest and lowest quintile of physical activity among women in the Nurses’ Health Study was 0.44 ng/mL. The mean level at baseline was 1.92 +/- 0.91 ng/mL. In the Health Professionals Follow-up Study, the within person correlation for C-peptide over four years was 0.57. This yields a sample size of 79 subjects per group. We can assume the within person correlation over one year is higher. If the correlation rises to 0.73, the sample size is 50 subjects per group.

In a 12-week exercise study of lean men, Dekker et al reported a mean IL-6 level of 2.8 +/- 0.6 pg/mL at baseline and of 1.9 pg/mL at study end for a mean change of 0.9 pg/mL.^87^ Assuming a correlation of 0.85, this yields a sample size of 3 subjects per group. If the correlation drops to 0.5, the sample size increases to 10 subjects per group.

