Thus, based on our estimates, we estimate that 20 subjects per group is sufficient to detect differences in several of our outcomes, but not all. 50 subjects per group will provide sufficient power to detect differences in all our markers. However, as this is a pilot project we are not concerned with obtaining sufficient power in our outcomes and we will enroll 20 subjects (10 per group). We realize that participant drop out may prohibit our ability to detect differences in some outcomes, but as noted above, **this is a pilot feasibility study**.

**C.11. Data analysis**.

**C.11.a. Primary Aim:** To conduct a dose response pilot trial of low (30 min/day) or high (60 min/day) dose exercise in men and women at increased risk of colon cancer. The major outcomes are changes in serum levels of four risk-related biomarkers: insulin, C-peptide, IL-6 and PGE-2.

Hypothesis 1.1: First we will evaluate randomization success by comparing the two intervention groups on demographic and health factors. We will then evaluate intervention effects by differences in biomarker levels at study end between intervention groups using linear regression. We will compare differences in mean change in each of the biomarkers from baseline to three months between intervention groups. The analysis is based on change over three months using mixed effects regression models with PROC MIXED of SAS. The model is:

Y_it_ = α + β_1_t + β_2_X_i1_ + β_3_X_i1_t + β_4_tY_i0_ + e_it_

where Y_it_ = biomarker for subject i at time t, where t = 0 for baseline, t = 1 for 3 months.

X_i1_ = 1 if i^th^ subject is in the Plus intervention group, = 0 otherwise; e_it_ ~ N(0, σ^2^)

Of primary interest is β_3_ = mean difference in biomarker level change between intervention groups. The coefficient β_2_ allows for mean differences in level between groups at baseline. The coefficient β_4_ allows the change in biomarker to depend on initial level. We will conduct unadjusted analyses because of the randomization design but will also examine the effects of adjusting for sociodemographic factors, and family history of colon cancer. We will conduct outcome analyses based on assigned treatment at randomization regardless of adherence (intent to treat analysis). Throughout our analyses missing data will be imputed.^139^

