**C.11.b. Secondary Aim: To compare changes in the secondary outcome of physical activity over three months.**

Hypothesis 2.1: We will evaluate the intervention effectiveness at changing physical activity levels by comparing change in average step count recorded on blinded pedometers from baseline to follow up between the intervention groups. Mixed effects regression will be used to account for the longitudinal design. The outcome variable will be the average steps per day for the measurement period. The measurement period at baseline and follow-up is the seven day period participants were required to wear the blinded pedometer. Only days where the participant wore the pedometer for at least eight hours will be counted and the average will be based on the number of full days of wear. The analysis is based on change using mixed effects regression models similar to that outlined in Aim 1. We will also examine the percentage of intervention participants meeting the 10,000 and 13,000 steps per day goals at the study conclusion based on data recorded on the pedometer. We will use the last seven days of the phase. We will also examine the percent of participants adhering to their study arm prescription (defined as completing 90% of required physical activity) at three months. We will examine whether sociodemographic factors, overall physical activity level, or family history of colon cancer are associated with meeting the intervention step count requirement. Finally, we will examine whether the intervention changed total physical activity levels by comparing baseline and follow-up total physical activity levels (as measured by the PPAQ) in the intervention groups and by comparing change in those levels between the intervention groups using the general estimating equation modification to linear regression.

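### Change in PPAQ total physical activity is assigned to GEE with only 20 participants; run in its usual form at an assumed 5% level, the between-arm test would reject about 8% of the time under the null

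*Protocol*

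**What the plan says.** Protocol section C.11.b (Secondary Aim) first deals with the blinded-pedometer step count, which is analysed by mixed effects regression. Its last item turns to total physical activity. The intervention is to be assessed "by comparing baseline and follow-up total physical activity levels (as measured by the PPAQ) in the intervention groups", and also by comparing the change between the groups, "using the general estimating equation modification to linear regression".

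Sections C.4 and C.9 fix the size: 20 participants, randomised equally, 10 per arm. The change model in C.11.a has two time points, "where t = 0 for baseline, t = 1 for 3 months".

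For the PPAQ analysis the protocol states no variance estimator, working correlation, reference distribution or significance level. The only alpha in the document belongs to the insulin sample-size calculation in C.9, "using a Bonferroni correction with two-sided 0.05/2 = 0.025".

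**The concern.** GEE inference is usually made with the empirical (sandwich) variance and a normal reference. Both are justified as the number of independent units grows. Here the independent units are 20 participants for the between-arm comparison and 10 for each within-arm comparison.

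Two small-sample errors act in the same direction. The uncorrected sandwich divides by n where an unbiased variance divides by n − 1, and the statistic is compared with 1.96 instead of a t quantile. P-values come out too small and intervals too narrow. At stake are an over-ready claim that the higher dose changed total activity, or that activity rose within an arm, and an overstated precision if the pilot estimates are used to plan a larger trial.

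**Working it through.** The protocol gives no type I error for this test, so there is no figure of its own to reproduce.

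**Inputs**
- n = 10 per arm, 1:1 allocation (C.4, C.9).
- Two visits per participant (C.11.a).
- Complete data after imputation (C.11.a: "Throughout our analyses missing data will be imputed").
- Assumed, because not stated for this test: two-sided 5%, uncorrected sandwich variance, normal reference.
- Data assumed normal in the main calculation; lognormal data checked by simulation.

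**Between-arm contrast (arm by time)**

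With two visits, complete data and equal arms, the GEE estimate is the difference in mean change. Its uncorrected sandwich variance is the sum over the two arms of [(n − 1)/n] · s²/n, where s² is the usual sample variance of change in that arm. The ordinary two-sample t statistic uses s²/n. Therefore

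z(GEE) = t(2n − 2) · √(n/(n − 1)).

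Rejecting when |z| > 1.96 is the same as rejecting when |t(18)| > 1.96 · √(9/10) = 1.859, and P(|t(18)| > 1.859) = 7.9%.

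Simulation of this statistic (100,000 trials, within-person correlation 0.5) gave 8.1%. Fitting GEE by software with an exchangeable working correlation gave 9.1% in 1,500 trials (Monte Carlo SE about 0.7 points) and 7.3% in 3,000 trials (SE 0.5 points), one on each side of the exact value. With lognormal data the uncorrected form gave 6.5%.

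**Within-arm test, baseline to follow-up**

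The same inflation applies with n − 1 = 9 degrees of freedom: P(|t(9)| > 1.859) = 9.6%.

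**How far the between-arm result depends on the implementation** (normal data, 10 per arm, nominal 5%)

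| Variance | Reference | True size |
|---|---|---|
| Uncorrected sandwich | normal | 7.9% |
| Uncorrected sandwich | t(18) | 6.2% |
| Unbiased (n − 1) | normal | 6.6% |
| Unbiased (n − 1) | t(18) | 5.0% |
| Mancl-DeRouen | normal | 5.4% |
| Mancl-DeRouen | t(18) | 4.0% |

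**Interval width relative to uncorrected sandwich with normal reference**
- Unbiased variance, t(18): (2.101/1.96) · √(10/9) = 1.13.
- Mancl-DeRouen, t(18): this correction multiplies the uncorrected standard error by 10/9 for this contrast, so (2.101/1.96) · (10/9) = 1.19.
- Within arm, paired t(9): (2.262/1.96) · √(10/9) = 1.22.

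**The case against.** The strongest reply is that the protocol names only GEE. A reader might infer that it prescribes standard robust errors and so carries a true error rate near 8%. The text does not support that: a corrected sandwich with a t reference is compatible with the sentence as written, and such details are commonly left to a statistical analysis plan, which is not at hand. This stands. The 8% is conditional, and across the implementations tabulated the size runs from about 4% to about 8%. What remains is the choice the protocol does make, a large-sample method for 20 people with nothing said to adapt it.

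Three further inferences should be resisted.
- **That false positives are some 60% more frequent than stated.** No error rate is stated for this test; 5% is an assumption.
- **That drop-out makes it worse.** The size would rise to 8.3% at 9 completers per arm and 8.8% at 8, but only in a completer analysis. C.11.a says missing data are imputed, and no drop-out rate is given.
- **That the protocol already holds the right model for its other outcomes.** C.11.a writes out a PROC MIXED model with baseline as one of the outcome rows and gives no method for degrees of freedom. It is not an ANCOVA with a t reference.

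It is also fair to say that GEE does not need the normal-error assumption written into C.11.a, which has some appeal for a self-report score. That advantage is itself a large-sample one and does not remove the small-sample bias of the variance.

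Finally, section C.3.c.1 describes the questionnaire as a supplement to the step counts, and C.9 says "as this is a pilot project we are not concerned with obtaining sufficient power in our outcomes". That limits the importance of the test. It excuses low power, but not intervals narrower than their label.

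**Conclusion.** The point holds as a minor, conditional one. If GEE is run with the uncorrected sandwich and a normal reference at a two-sided 5%, with 10 complete participants per arm, the between-arm test has a true size of 7.9% with normal data and about 6.5% with lognormal data. A within-arm test has 9.6% with normal data. If a small-sample correction and a t reference are already planned elsewhere, the problem is absent.

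No primary conclusion rests on this analysis. The declared secondary outcome, pedometer steps, is analysed by another method and is not touched.

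**What to change.** Replace the GEE clause in C.11.b by one of two specifications.

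1. **Preferred:** a linear model for PPAQ follow-up or change, with arm and baseline PPAQ as covariates and a t reference (20 − 3 = 17 residual degrees of freedom with complete data). Use a paired t test for change within each arm.
2. **If GEE is kept:** name a small-sample-corrected sandwich variance, for example Mancl-DeRouen, and a t reference.

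In either case state the significance level.

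The change is to the analysis text only and needs no new data. Its price is wider intervals: about 13% between arms with the unbiased variance and t(18), before any gain from baseline adjustment, and about 22% within an arm with the paired t. Mancl-DeRouen with t(18) costs about 19% between arms and is slightly conservative (4.0% under normal data), which is why the linear model is the better choice.

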**D. Data Safety and Monitoring**

Participants will be identified in data records by a study ID code to protect data. Identifiable information will be kept separate from study data and will be locked in a study file cabinet. Electronic files will not contain identifiable participant information. Identifiable information will be destroyed at the end of the study.

All investigator-level staff members have completed the NIH human subject’s certification as required. All study field staff, investigators, and others involved with participants and/or data collection and handling will have completed the NIH human subjects’ certification as required. Human subjects concerns will be a standard agenda item for project meetings. We will participate in a standard continuing review process. All adverse events reported to study staff or investigators will be discussed by the investigators. Investigators will evaluate the potential risk to other participants.

The principal investigator will review all patient data at least every six months, and provide a semi-annual report to the QASM Committee. This report will include

1. the protocol title, IRB protocol number, and the activation date of the study.
2. the number of patients enrolled to date
3. the date of first and most recent patient enrollment
4. a summary of all adverse events regardless of grade and attribution
5. a response evaluation for evaluable patients
6. a summary of any recent literature that may affect the ethics of the study.

The study principal investigator and study coordinator will monitor for toxicities/adverse events on an ongoing basis. Once the principal investigator or study coordinator becomes aware of a serious adverse event, the SAE will be reported to the HRPO and QASM Committee within 10 working days.

